### Recruitment

Eligible children will be identified from clinics at one of six sites (Brisbane, Darwin, Melbourne Perth and Sydney in Australia, and Auckland in New Zealand). Parents will be approached, and informed consent obtained. Baseline pre-exacerbation data will be collected (Figure 1), parents will be contacted monthly, and children will be reviewed every 3 months. Parents will be educated specifically on how to recognize the symptoms of an acute respiratory exacerbations, and asked to contact the research nurse at the onset of an exacerbation event.

### Intervention and follow-up

A double-dummy design is planned. If eligibility is fulfilled, and after informed consent has been obtained, the child will be randomized to one of two arms. At the start of the exacerbation, the child will receive orally: 1) azithromycin with placebo amoxycillin-clavulanate or 2) amoxycillin-clavulanate with placebo azithromycin. The azithromycin dose is 5 mg/kg/day (to a maximum of 200 mg daily, and for amoxycillin-clavulanate it is 22.5 mg/kg/dose twice daily (maximum 900 mg/dose). Equivalent volumes of placebo will be given for both trial medications. All treatments will continue for 21 days.

An exacerbation is defined as an increase in sputum volume or purulence, or change in cough (>20% increase in cough score [46] or type (dry to wet) [47]) for more than 3 days. We validated this definition in our prospective study, and found that the kappa values (between clinicians) of these symptoms and signs were excellent (>0.75) [48]. Daily diaries will also be collected during exacerbations until the scores for 2 or more days reflect the child’s baseline state, which for each child will be established at enrolment, prior to any exacerbations. This assessment consists of a combination of symptoms (daily cough (yes/no), cough quality (wet/dry/none), cough score [46] averaged over two consecutive days) and signs (sputum color (if any present) using a color chart card (BronkoTest Ltd, London, UK), and crackles on chest auscultation). Children will be reviewed on days 14 and 21, and at resolution of the exacerbation. The exacerbation is considered resolved when symptoms and signs are the same as the baseline state. Post-exacerbation, the children will be followed up and evaluated clinically every 3 months for a period of 18 months or until their next exacerbation (whichever is sooner). The time to next exacerbation will be determined by duration of days from the resolution of the current exacerbation to the beginning of the next exacerbation.

### Randomization, allocation, and blinding

Upon enrolment, the child will be assigned to the next unique number on the appropriate stratified list. The allocation will be performed by the trial pharmacist at the Royal Children’s Hospital (Brisbane, Australia). Randomization is stratified by site (Brisbane, Darwin, Melbourne, Perth, Sydney, Auckland), age (≤5 or >5 years) and underlying etiology (idiopathic/post-pneumonia or all other causes). The randomization sequence is computer-generated and uses permuted blocks. The allocation sequence will be concealed at all times throughout the study. The computer-generated allocation sequence was prepared by a statistician external to the study team.

The specially manufactured placebo medications (Institute of Drug Technology Australia Ltd, Melbourne, Victoria, Australia), have a similar taste and color to their respective antibiotics. Both active medications (azithromycin and amoxycillin-clavulanate) will be repackaged and relabeled so that both antibiotics and their respective placebos are provided in identical opaque bottles. For all trial medications, equal volumes of water are added using a syringe and needle by punching the seal. Adherence will be assessed by parent report and return of empty bottles.

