**Methods:**

This will be a multicenter, randomized, double-blind, double-dummy, placebo-controlled, parallel group trial involving six Australian and New Zealand centers. In total, 170 eligible children will be stratified by site and bronchiectasis etiology, and randomized (allocation concealed) to receive: 1) azithromycin (5 mg/kg daily) with placebo amoxycillin-clavulanate or 2) amoxycillin-clavulanate (22.5 mg/kg twice daily) with placebo azithromycin for 21 days as treatment for non-severe respiratory exacerbations. Clinical data and a parent-proxy cough-specific quality of life (PC-QOL) score will be obtained at baseline, at the start and resolution of exacerbations, and on day 21. In most children, blood and deep-nasal swabs will also be collected at the same time points. The primary outcome is the proportion of children whose exacerbations have resolved at day 21. The main secondary outcome is the PC-QOL score. Other outcomes are: time to next exacerbation; requirement for hospitalization; duration of exacerbation, and spirometry data. Descriptive viral and bacteriological data from nasal samples and blood inflammatory markers will be reported where available.

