### Sample size

We plan to enroll 170 children (85 per arm), providing 90% power (α = 0.05, 1-sided) with 20% non-inferiority margin to detect 80% resolution rate by day 21. The margin selected is relatively large in statistical terms, but the physicians considered it clinically appropriate. As the primary outcome will be obtained in all enrolled children, retention fraction has not been factored in for the intention-to-treat analysis.

The main secondary outcome (secondary aim 1) is PC-QOL. Based on a non-inferiority limit of 0.9 (minimum important difference [57]) and standard deviation of 0.9, our sample size provides a power of 99.9% (α = 0.05, one-sided 95% CI) for data from at least 136 children (assuming at least 80% retention of children enrolled). For secondary aim 2 (see list under ‘Aims of the study’), we will be examining eight main factors, and thus a sample size of 136 exceeds the recommended minimum (n = 10 per factor) [65]. The eight factors are: smoking, age, underlying etiology, detection of virus (any versus none, then single versus multiple viruses), presence of azithromycin resistance, and levels of various blood markers (IL-6, IL-10, IP-10).

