### Statistical analysis and reporting

Data will be reported and presented in accordance with the updated Consolidated Standards of Reporting Trials (CONSORT) criteria [66]. Children will be analyzed in accordance with allocation status (regardless of subsequent management).

For our primary aim, the main effects of the interventions will be determined by comparing the primary outcome (resolution of exacerbation) between groups (azithromycin versus amoxicillin-clavulanate). Children who exit the study as ‘clinically worse’ or ‘drop-out’ before the end point is reached will be considered as ‘non-resolved’. Those who exit the study as ‘returned to baseline’ will be considered as ‘resolved’. Odds ratios will be calculated and, if appropriate, the number needed to treat (for benefit) will be expressed. Per-protocol analysis will be an *a priori* secondary analysis.

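### Randomisation is stratified by site, age and etiology, but the analyses described use none of these factors; adjusting is a small, free gain, and the abstract should name all three stratifiers

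*Protocol article*

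**What the plan says.** Under Randomization, allocation, and blinding, the article states: "Randomization is stratified by site (Brisbane, Darwin, Melbourne, Perth, Sydney, Auckland), age (≤5 or >5 years) and underlying etiology". Etiology has two levels, and "The randomization sequence is computer-generated and uses permuted blocks". The Methods part of the abstract gives a shorter list: "170 eligible children will be stratified by site and bronchiectasis etiology". Age is absent there.

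Under Statistical analysis and reporting, the main effects "will be determined by comparing the primary outcome (resolution of exacerbation) between groups (azithromycin versus amoxicillin-clavulanate"). The effect measure follows: "Odds ratios will be calculated and, if appropriate, the number needed to treat (for benefit) will be expressed". That section names no covariate, model or confidence interval for the primary outcome.

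Under Statistical analysis for secondary outcomes and aims, continuous outcomes are assigned a t-test or a Mann-Whitney test according to normality. PC-QOL, the main secondary outcome, falls under this rule. Age and etiology reappear only under secondary aim 2, as candidate predictors of response that must first pass a univariate screen at P<0.2. Site does not reappear in the analysis.

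**The concern.** Stratified blocks make the arms more alike on the stratifiers than simple randomisation would. If those factors predict resolution, the treatment difference varies less from trial to trial than the usual two-sample standard error assumes. An analysis that ignores the factors then reports an interval wider than the data justify. In a non-inferiority trial the decision rests on one confidence bound, so unneeded width costs power.

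For PC-QOL the point is firmer, because the article names tests that cannot take covariates. For the primary outcome it rests on what is described: a comparison of two groups with no mention of the design factors.

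The two lists of stratifiers matter because an analysis that follows the design needs to know which factors were used. Two factors give 6 × 2 = 12 cells; three give 6 × 2 × 2 = 24.

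**Working it through.** **Inputs from the Sample size section:** 85 per arm, 80% resolution, margin 20 percentage points, one-sided alpha 0.05, 90% power. A true difference of zero is assumed.

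**The plan's own figure.** With unpooled variance, n per arm = (z₁₋α + z₀.₉₀)² × 2 × 0.8 × 0.2 / 0.2².
- One-sided 0.05: (1.645 + 1.282)² × 0.32 / 0.04 = 68.5, so 69 per arm (138 in total).
- One-sided 0.025: (1.960 + 1.282)² × 0.32 / 0.04 = 84.1, so 85 per arm (170 in total).

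The 170 therefore matches one-sided 0.025, not the stated 0.05. That is a separate matter, but it sets the baseline here. At the stated alpha, the crude standard error is √(0.32/85) = 0.0614 and power is Φ(0.2/0.0614 − 1.645) = 94.7%. At one-sided 0.025 it is 90.3%.

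**Cell size.** 170 / 24 = 7.1 children per cell on average.

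**Large-sample gain on the risk difference.** Let s be the standard deviation of resolution rates between strata. The article gives no value, so s is an assumption. The within-stratum variance is 0.16 − s², and the crude standard error is too large by the factor √(0.16/(0.16 − s²)). Power uses one-sided 0.05.

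| Assumed s | Within-stratum variance | Crude / stratified SE | Half-width of one-sided 95% bound | Power |
|---|---|---|---|---|
| 0 | 0.1600 | 1.000 | 10.1 points | 94.7% |
| 5 points | 0.1575 | 1.008 | 10.0 points | 95.0% |
| 10 points | 0.1500 | 1.033 | 9.8 points | 95.7% |
| 15 points | 0.1375 | 1.079 | 9.4 points | 96.9% |

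The largest gain in power is 96.9 − 94.7 = 2.2 points.

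**Check by simulation with sparse cells.** There were 6,000 trials per setting, 170 children spread over 24 cells, and permuted blocks of 4 (block size is not given, so this is assumed). Stratum effects were drawn on the logit scale. In the large-sample calculation, logit SDs of 0.5 and 1.0 correspond to about 8 and 15 points. The crude risk difference was compared with a Mantel-Haenszel risk difference over all 24 cells. Type I error was taken at a true difference of −20 points.

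| Logit SD | Crude / stratified half-width | Power, crude v stratified | Type I error, crude v stratified |
|---|---|---|---|
| 0 | 0.99 | 95.0% v 94.6% | 5.1% v 5.1% |
| 0.5 | 1.01 | 95.1% v 95.1% | 4.7% v 4.9% |
| 1.0 | 1.06 | 95.2% v 96.4% | 3.9% v 5.0% |

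At logit SD 1.0 with no true difference, the crude and stratified estimates had the same simulated standard deviation (0.0587), while the mean crude half-width implies a standard error of 0.1008/1.645 = 0.0613. The design already delivers the precision; the crude standard error does not show it.

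**PC-QOL.** With the stated limit of 0.9, SD of 0.9 and 136 children (68 per arm), power is Φ(0.9/(0.9 × √(2/68)) − 1.645) = Φ(5.83 − 1.645), above 99.9%, in line with the article's 99.9%. Adjustment there sharpens the interval but cannot add useful power.

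**The case against.** The strongest objection is that the article never calls the primary comparison crude or unadjusted. A reader might infer that it does, but the text gives only a between-group comparison and an odds ratio, and covariates are commonly settled in an analysis plan that is not shown here. This stands. For the primary outcome one can say only that no adjustment is described. It does not dispose of PC-QOL, for which the named tests leave no room for the factors.

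A reader might also infer that the planned interval is too wide or the trial short of power. The documents do not support that. No primary interval is defined and no stratum rates are given, so the size rests wholly on an assumed spread. The upper value is demanding, since one SD of 15 points above 80% is already 95%. With equal rates, stratifying over 24 sparse cells is slightly worse (ratio 0.99). At the stated alpha, crude power is above the 90% target.

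Nor do incomplete blocks make the crude analysis invalid. Each stratum has at most one unfinished block, and simulated crude type I error was 3.9% to 5.1%, nominal or conservative, so a false claim of non-inferiority is not favoured.

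Finally, the gain applies to the risk difference. On the odds-ratio scale that the article names, adjusting for prognostic strata generally does not narrow the interval, because the odds ratio is non-collapsible. This also stands, but the 20% margin is used in the sample size as a difference in proportions, so the risk difference is the relevant scale.

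**Conclusion.** The point holds as a modest, free improvement and not as a validity defect. Three factors shape the randomisation and none is used in the treatment comparisons described. If the strata predict resolution, an unadjusted analysis is valid but somewhat conservative: the crude standard error of the risk difference is about 1% to 8% too large for assumed between-stratum SDs of 5 to 15 points, and not too large at all if rates are equal. At one-sided 0.05 the gain in power is at most one or two points on about 94.7%; in the sparse-cell simulation it ran from −0.4 to +1.2 points. These figures assume 80% resolution in both arms and, in the simulation, blocks of 4.

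The abstract's omission of age is a real inconsistency but a clerical one. The Methods give the levels and the age cut-point and can be taken as the operative list, subject to the sponsor's confirmation.

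**What to change.** 1. Estimate the primary risk difference with one named estimator that accounts for the randomisation factors. One suitable choice is a logistic model with treatment and main effects for site, age group and etiology, followed by marginal standardisation. Do not stratify over the 24 cells directly. Report the unadjusted risk difference as a sensitivity analysis.
2. For PC-QOL, replace the choice between t-test and Mann-Whitney test with a linear model containing treatment and the same three factors.
3. Align the abstract with the Methods so that one set of stratifiers is named, checked against the randomisation lists already in use.

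The cost is wording alone. The stratum of each child is already in the randomisation records, and neither sample size nor data collection changes.

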### Data collection

All data will be recorded on standardized forms. On enrolment, demographic information (including age, gender, ethnicity, and household size), birth history, breast-feeding history, prior illness, and *in utero* and household smoke exposure, will be recorded, and a physical examination will be performed by a study physician. The primary and secondary outcome measures will be collected at the time points specified above. Serious and non-serious adverse effects (AEs: nausea, vomiting, diarrhea, rash) will also be documented and monitored. Safety exit points are discussed under ‘End points’ below.

### Specimen collection

At enrolment (baseline) all children will have a deep-nasal swab (NS) specimen collected. In a subset, additional specimens will be collected at baseline and during exacerbations, depending upon feasibility (some children may be unable to attend the study center at the onset of the exacerbation) and willingness of parents to allow additional NS collections and venepuncture procedures to be performed. These specimens are:

A deep NS specimen for respiratory viruses, respiratory bacterial pathogens (including antibiotic susceptibility testing), and other potentially important respiratory pathogens (*M. pneumoniae, Chlamydiales* spp) at baseline, and at the beginning and resolution of an exacerbation. The techniques used are identical to previous studies [49-51], in which the specimens were described as nasopharyngeal swabs. In this study, we have elected to call these specimens ‘deep-nasal swabs’ as it is anatomically accurate to do so. The NS specimens will be handled in accordance with our research laboratory protocol (see below).

Blood samples will be taken at baseline and at the beginning and end of each exacerbation for determination of C-reactive protein (CRP), interleukin (IL)-6 (a neutrophilic marker of inflammation [52]), serum amyloid A (SAA) [48], and markers of viral infection (IL-10, interferon γ-inducible protein (IP)-10) [53].

Sputum samples will also be taken at baseline and at the beginning and end of each exacerbation (when possible) for lower-airway microbiology cultures and antibiotic sensitivity tests.

### Further description of scores and laboratory methods

#### Cough score

The verbal categorical descriptive score is a validated daily diary score of cough rated on a six-point scale (0 (no cough) to 5 (severe cough and cannot perform usual activities)) with increasing scores reflecting greater interference with usual activities. This rating was validated against an objective cough-meter measure [46], and changes in cough scores have been shown to reflect changes in objective cough counts [54].

#### Parent-proxy cough-specific quality of life score

The parent-proxy cough-specific quality of life (PC-QOL) score is a 27-item questionnaire designed to assess the level of frequency of feelings (15 items) and worry (12 items) related to their child’s cough. It uses a seven-point Likert-type scale, with higher scores reflecting less frequency and fewer worry concerns (that is, greater QOL) [55,56]. The minimal important difference is 0.62 as determined by the distribution method, and 0.9 as determined by the anchor method [57].

#### Bacteriology of nasal swab

Compared with NS, oropharyngeal sampling underestimates *Streptococcus pneumoniae* carriage by approximately 50% [58], Thus NS is the preferred method when evaluating the presence of antibiotic-resistant bacteria. Culturing, identifying, and when appropriate, serotyping common respiratory bacteria are established techniques in our research laboratory [51,59]. Swabs are stored in skim-milk tryptone-glucose-glycerol broth medium at −80°C ,before being batch-processed for typical respiratory bacterial pathogens, notably *S. pneumoniae*, *H. influenzae (*including strains of non-typeable *H. influenzae)* and *Moraxella catarrhalis.* Batches of swabs are thawed, and 10 μL aliquots cultured overnight on selective media at 37°C in 5% CO_2_. Growth of *S. pneumoniae*, *H. influenzae* and *M. catarrhalis* is recorded and confirmed by standard techniques [51,60]. Two isolates each of *S. pneumonia**H. influenzae* and *M. catarrhalis* per positive swab are tested for anti-microbial resistance and stored [51,60]. *S. pneumoniae* isolates are serotyped using the Quellung method (antisera from Statens Serum Institute, Copenhagen, Denmark). Routine susceptibility testing using the calibrated dichotomous susceptibility disk-diffusion method. If the if the azithromycin disk annulus is less than 6 mm the minimum inhibitory concentration (MIC) of azithromycin will also be determined (Etests; AB Biodisk, Solna, Sweden). For *S. pneumoniae*, the penicillin MIC will be determined for penicillin non-susceptible isolates (oxacillin and/or penicillin disk annulus < 6 mm) and for *H. influenzae*, the ampicillin MIC will be determined for ampicillin non-susceptible isolates (ampicillin disk annulus < 6mm). Interpretive criteria (Clinical and Laboratory Standards Institute breakpoints) used for *S. pneumoniae* are penicillin non-susceptible MIC greater 0.12 μg/ml and azithromycin resistance MIC 2 μg/ml or greater; and for *H. influenzae*, ampicillin resistance MIC 4 μg/ml or greater and azithromycin resistance MIC greater than 4 μg/ml. A nitrocephin-based test will identify beta-lactamase activity in *H. influenzae* and *M. catarrhalis* isolates.

#### Assessment for viruses and other bacteria

We will use our previously described methods of assessment [61,62]. Nucleic acids will be extracted from the media (High Pure Viral Nucleic Acid Kit; Roche Diagnostics, Sydney, NSW, Australia), in accordance with the manufacturer’s instructions. Real-time PCR assays will be used to detect respiratory syncytial viruses (A and B), adenoviruses, influenza viruses (A and B), parainfluenza, human metapneumovirus, human coronaviruses (OC43, HK1, 229E, and NL63), enteroviruses, rhinoviruses (including determining specific rhinovirus genotypes by sequencing the VP4-VP2 region [63]) and the more recently described human viruses (human bocavirus 1, parechoviruses, and human polyomaviruses K1 and WU) and *M. pneumoniae* and *Chlamydiales* species [64].

#### Blood markers

CRP, threshold 5 mg/l) are standard tests that will be analyzed by the Diagnostic Laboratories of each participating center. SAA, IL-6 (threshold <3 pg/ml), IL-10 (threshold <0.5 pg/ml) and IP-10, (threshold 2.8 pg/ml) will be performed by commercial enzyme immunoassay kits (R&D Systems, Minneapolis, USA) at our research laboratory.

Spirometry (in children aged ≥5 years) will be performed using American Thoracic Society criteria and the recorded FEV_1_ % predicted. We elected not to use oscillatory measures, as we previously found no difference in airway resistance between steady and exacerbation states [48]. Thus, we will use conventional spirometry, although we do not expect to detect significant differences.

### End points

Participation will be complete when the child’s clinical state returns to baseline and the time to next exacerbation has been obtained. Other exit points are: if the child deteriorates during treatment prior to day 21, or becomes sufficiently intolerant of the trial medications to require withdrawal from the study (as determined by the treating clinician).

### Outcome measures

#### Primary outcome

The primary outcome will be the proportion of children whose exacerbations have resolved by day 21 of treatment. Exacerbations will be considered resolved when symptoms and signs are the same as the baseline state. Children who are withdrawn from the study, or receive additional antibiotic treatment, will be categorized as non-resolved.

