#### Secondary clinical outcomes

The main secondary outcome is the PC-QOL score. Other outcomes are 1) the time to next exacerbation; 2) requirement for hospitalization; 3) duration of exacerbation (persistence of symptoms till return to baseline state); and 4) FEV_1_ % predicted.

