#### Statistical analysis for secondary outcomes and aims

For the clinical secondary outcome (secondary aim 1), the *t*-test or the Mann–Whitney test will be used for continuous variables (depending on normality of data distribution). A Kaplan-Meier curve will be constructed for each group for time to resolution and time to next exacerbation, as reported previously [67]. For secondary aim 2 (factors that predict response to antibiotics), univariate analyses will be used to examine several biologic factors (for example, smoking, age, ethnicity, underlying etiology, detection of virus (any versus none, then single versus multiple viruses), presence of azithromycin resistance, and levels of blood markers (IL-6, IL-10, IP-10)). Factors with *P*<0.2 will be included in a logistic regression model. Potential interactions (for example,. between viruses and bacteria) will be examined in the model. Descriptive data will be used for secondary aim 3 (point prevalence of respiratory pathogens).

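### The two coding rules for the primary outcome disagree about a child who receives an additional antibiotic and is back at baseline by day 21

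*Protocol article*

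**What the plan says.** The protocol article gives the coding of the primary outcome twice.

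- **Outcome measures, Primary outcome.** After defining resolution as symptoms and signs matching the baseline state, it adds: "Children who are withdrawn from the study, or receive additional antibiotic treatment, will be categorized as non-resolved". Withdrawal and additional antibiotics are two separate grounds for failure.
- **Statistical analysis and reporting**, in the paragraph on the primary aim. Failures are described as follows: "Children who exit the study as ‘clinically worse’ or ‘drop-out’ before the end point is reached will be considered as ‘non-resolved". Successes follow: "Those who exit the study as ‘returned to baseline’ will be considered as ‘resolved". Additional antibiotics are not mentioned, and the success category has no exception.

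Two other statements bear on how far these rules differ. The End points section lists as an exit "if the child deteriorates during treatment prior to day 21", and also lists intolerance that requires withdrawal. The analysis section opens with "Children will be analyzed in accordance with allocation status (regardless of subsequent management").

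**The concern.** Consider a child who receives an additional antibiotic on day 10, is not withdrawn, and is back at baseline on day 17. Under the Primary outcome section the child is non-resolved. Under the analysis section the child has returned to baseline and is resolved. Two analysts, each following a published sentence, would enter different values for the same child.

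The direction of the discrepancy matters because this is a non-inferiority trial. An arm with more failures has more children who can be rescued. Counting rescue cures as successes therefore lifts the weaker arm more and narrows a real deficit, even when rescue is used in the same proportion of failures in both arms.

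**Working it through.** **Step 1. Set the rules side by side.**

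| Child | Primary outcome section | Statistical analysis section |
|---|---|---|
| Withdrawn for intolerance, or drops out | Non-resolved | Non-resolved (drop-out) |
| Deteriorates before day 21 and exits | Non-resolved (withdrawn) | Non-resolved (clinically worse) |
| At baseline by day 21, no additional antibiotic | Resolved | Resolved |
| Additional antibiotic, not withdrawn, at baseline by day 21 | **Non-resolved** | **Resolved** |

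Only the last row conflicts.

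**Step 2. Inputs.** The Sample size section gives 85 per arm, one-sided alpha 0.05, a 20% margin (taken as 20 percentage points), 80% resolution and 90% power. The protocol gives no rescue rate. I write *f* for the share of failures in each arm who are rescued, back at baseline by day 21 and counted as resolved. It is an assumption, taken over 0 to 0.3.

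**Step 3. The plan's own figure.** With 80% in both arms and the unpooled normal approximation, n per arm = (z_alpha + z_beta)² × (0.16 + 0.16) / 0.20² = 8 × (z_alpha + z_beta)².

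- One-sided 0.05: 8 × (1.645 + 1.282)² = 68.5, so 69 per arm. At 85 per arm the power is 94.7%.
- One-sided 0.025: 8 × (1.960 + 1.282)² = 84.1, so 85 per arm. The power is 90.3%.

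The stated 85 fits one-sided 0.025 and not the printed 0.05. The present point does not rest on this, but I show both levels below.

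**Step 4. Effect of recoding, with the true difference at the margin.** Take true resolution without rescue of 80% on amoxycillin-clavulanate and 60% on azithromycin.

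- Apparent rates: 0.80 + 0.20*f* and 0.60 + 0.40*f*.
- Apparent deficit: d = 0.20 × (1 − *f*).
- SE = √{[p₁(1 − p₁) + p₂(1 − p₂)] / 85}.
- P(declare non-inferiority) = Φ[(0.20 − d)/SE − z].

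For *f* = 0.2 the rates are 0.84 and 0.68, and d = 0.16. SE = √[(0.1344 + 0.2176)/85] = 0.0644, so (0.20 − 0.16)/0.0644 = 0.62. Then Φ(0.62 − 1.645) = 0.153.

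| *f* | Apparent rates | Deficit (points) | False non-inferiority, one-sided 0.05 | One-sided 0.025 |
|---|---|---|---|---|
| 0 | 80% v 60% | 20 | 5.0% | 2.5% |
| 0.1 | 82% v 64% | 18 | 8.9% | 4.8% |
| 0.2 | 84% v 68% | 16 | 15.3% | 9.0% |
| 0.3 | 86% v 72% | 14 | 25.1% | 16.2% |

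In children, failures number 0.40 × 85 = 34 and 0.20 × 85 = 17. So *f* = 0.1 means recoding about three children in one arm and two in the other.

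**The case against.** The strongest reply is that the Primary outcome section is the definition, and the analysis section says that it compares that outcome. On this view the later text is an incomplete restatement and overrides nothing. That stands. A reader might infer that the protocol credits cures by rescue treatment to the randomised drug. The document does not support this: its explicit definition forbids it, and under that definition the inflation in the table is zero.

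Second, the exits under End points narrow the gap. Children who deteriorate, or who become too intolerant to continue, are failures under both rules. This also stands, and it would lower *f*. It does not empty the conflicting group, because the outcome definition names additional antibiotics separately from withdrawal and so provides for rescued children who remain in the trial.

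Third, the analysis rule speaks of children who exit, and the child in the example stays in. This carries less weight. End points treats return to baseline as part of ordinary completion, so returned-to-baseline is the only category in the analysis rule that fits such a child. The statement on analysis by allocation does not decide the matter either, since it concerns the analysis set and not the coding of the outcome.

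A reader might also extend the point to the secondary outcomes, where duration is defined as "duration of exacerbation (persistence of symptoms till return to baseline state") and the plan says "A Kaplan-Meier curve will be constructed for each group for time to resolution and time to next exacerbation". Neither has a rule for rescue. That is not a contradiction. Time to actual return to baseline, whatever further treatment is given, is a legitimate estimand, and a day-21 curve height that differs from a composite primary proportion is no error. Event and censoring rules are commonly left to an analysis plan, which is not shown here. Never counting rescued children as resolved would also remove the start date for time to next exacerbation, which Intervention and follow-up measures from resolution.

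**Conclusion.** The point holds for the primary outcome only. The two coding rules give opposite values for a child who receives an additional antibiotic, is not withdrawn and is back at baseline by day 21. Nothing in the article says which section prevails, although the outcome definition is the more explicit of the two.

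The possible size is material. At a true deficit equal to the margin, false non-inferiority would rise from 5% to about 9%, 15% or 25% for *f* of 0.1, 0.2 or 0.3. This needs the analysis wording to be applied in place of the definition, equal rescue shares in both arms, a normal-approximation test of the risk difference, and rescue shares that the protocol does not give. The figures show what the ambiguity could cost; they do not estimate this trial's error rate. The wording should be corrected, but the design is not undermined.

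**What to change.** In Statistical analysis and reporting, qualify the success category: an exit as returned to baseline is coded resolved only if baseline was reached by day 21 without additional antibiotic treatment. Add additional antibiotic treatment to the list of grounds for non-resolved, so that the list matches the Primary outcome section.

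The cost is one clause, best added before unblinding. The data are already needed to apply the outcome definition, and the sample size is unaffected. The change concerns outcome coding only and does not touch when or how additional antibiotics are given. No change to duration or time to resolution is needed on this ground.
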